**Figure 3 F3:**
[figure not shown]
Diagram of a valid instrumental variable (IV). NICU, neonatal intensive care unit.

A potential IV, used in previous studies in the USA,^26 30^ is the difference of the distances of the mother residential postal code to the nearest NICU and LNU postal codes (excess distance). This has the potential to be an appropriate IV because of:

(1) Association with delivery in NICUs (refers to the arrow from IV to NICU in figure 3). Previous studies suggest that a high-risk mother is more likely to deliver in NICU if she is living close to an NICU hospital.^26^

(2) No direct effect on outcomes (refers to the crossed line from IV to outcome in figure 3). The assumption that the difference in travel times to either facility should not directly affect the outcomes except through the route of whether the baby is born in an NICU hospital,^29^ (3) independence of unmeasured confounding factors (refers to the crossed line from IV to UC in figure 3). This is based on the assumption that mothers do not choose where to live based on distance to a high-level NICU, since preterm delivery is usually not expected before pregnancy. However, because hospitals with NICUs tend to locate in select areas (ie, cities), mothers who live here may be different from those who do not, in terms of socioeconomic characteristics. We attempt to address this issue by controlling for mothers’ occupation and deprivation.

Analysing healthcare costs and cost-effectiveness outcomes: A cost analysis with a UK NHS perspective will be conducted. The cost of neonatal care received by preterm babies in NICU and LNU up to hospital discharge will be estimated. Standard care package in neonatal units will be costed by level of care, as categorised by the six Healthcare Resource Groups (HRG) as listed in table 1. HRGs are defined to group the use of healthcare resources of clinically similar treatments for costing purposes, and each of them is attached a unit cost that gives the average cost to the NHS of providing defined services to NHS patients in England. Unit costs used in our economic evaluation will be extracted from the NHS Reference Costs 2017/2018.

**Table 1 T1:** Reference cost for neonatal critical care—year 2017/2018—NHS England^14^

HRG codes	Types of care	National average unit cost (2017–2018)
XA01Z	Neonatal critical care, intensive care	£1445
XA02Z	Neonatal critical care, high dependency care	£925
XA03Z	Neonatal critical care, special care, carer not resident alongside baby	£605
XA04Z	Neonatal critical care, special care, carer resident at cot side and caring for baby	£435
XA05Z	Neonatal critical care, normal care	£441
XA06Z	Neonatal critical care, transportation	£1159

HRG, Healthcare Resource Group; NHS, National Health Service.

The costs of standard care provided by NICU or LNU, unit costs will be multiplied by the number of days using different levels of care. Since the standard packages costed by HRG codes do not include all major clinical activities, we will also cost the use of selected relevant procedures. These will include nitric oxide, surfactant replacement, total parental nutrition, ultrasound scanning, blood transfusion and palivizumab therapy. Cost data for these activities will be obtained from literature reviews and extracted from selected hospital finance departments as needed. The cost of surgical procedures are included in the standard care package by the level of care defined by HRG codes and will not be costed separately. Key components of healthcare resource use will be presented separately from associated costs as currently recommended.

Original neonatal care information will be linked to HES to extend the time horizon of the economic evaluation to 1 year of corrected age. A comprehensive cost analysis using the methodology above will be conducted to identify whether patterns of service use of hospital admissions, outpatient visits and accident and emergency services differs across neonatal strategies at 1-year-follow-up.

The number of lives saved will be the health outcome measure that will be used in the economic evaluation. Deaths occurring after discharge from the neonatal unit will be informed by the ONS linked. An incremental analysis of costs and health outcomes between NICUs and LNUs will be conducted and synthesised using the net-benefit framework. Current thresholds of willingness to pay as recommended by the National Institute for Health and Care Excellence (NICE) will be used to determine value for money.

We will follow current guidance for methods of technology appraisal to present and report the results of the economic analysis.^31–33^

### Workstream 2

Adjusting for heterogeneity within the types of units studied: Using NNRD data and augmented with novel evaluation of the quality of care provided in neonatal units through a PhD project, other parameters such as associations with volume and calibre of work undertaken, medical and nursing staffing, and comparisons against national neonatal auditable standards (using variables such as normal temperature measured within the first hour of life, receipt of breast milk on discharge, parental consultation within the first 24 hours, parent presence on ward round, blood stream infections, among others), will be explored in workstream 2. This information, along with information about the population of babies which are cared for at their unit (but not including outcomes), will be used to undertake a cluster analysis. This analysis will provide groups of units which are similar in terms of their characteristics and the care they provide, irrespective of their designation. The identified variables will be assessed in two ways:

They will be incorporated into workstream 1 as confounding variables to analyse potential heterogeneity between units, and to investigate to what extent they help to explain this.They will be used independently, in isolation and conjunction, to investigate associations with gestation-specific outcomes.

### Workstream 4

Understanding parent and clinician perspectives on decisions about place of care: Observations will explore: (1) factors that parents think should guide decision-making about place of care for babies, and how this happens in practice, (2) clinicians’ perspectives and practices around decision-making about place of care, (3) the impact on parents and families of this decision, and subsequent changes in care location and (4) how parents can best be supported.

Periods of observation within neonatal units will be completed, along with interviews with both clinicians and parents. An experienced qualitative researcher will observe relevant discussions and interactions that take place between parents and clinicians regarding place of care. Observations will be guided by an observation framework, developed through discussions with the project team and project parent panel. The observer will take written notes unobtrusively and will then debrief these either alone or with another member of the team. These debrief sessions will be audio recorded and transcribed.

Alongside observations, interviews will be conducted with parents and clinicians on their perspectives and experiences of decisions regarding place of care. We will also interview a separate group of parents about their retrospective experiences of having had a baby receive neonatal care in the past 12 months. Interview topic guides will be developed and piloted through discussions with the project team and parent advisory panel. Interviews will be audio recorded and transcribed verbatim.

Participants, who are willing and able to give informed consent, and are caring (or did care) for a baby born between 27 and 31 weeks gestation, will be included. Participation will be voluntary and it will be made clear to parents in particular that declining will not compromise the care they or their babies receive. Informed consent for participation will be obtained (written for formal interviews and verbal for observation).

We will conduct up to 40 interviews with parents and clinicians. Twenty interviews will be ‘retrospective’ interviews with parents whose babies had been discharged in the last 12 months. These will be selected from the 15 operational delivery neonatal networks in England. This will be undertaken through an open national advertisement for parents to participate, through the national parent charity for sick and preterm babies, BLISS. We will attempt to recruit a diverse sample of parents with babies born at different gestations between 27 and 31 weeks, parents for whom this is a first or subsequent pregnancy, and parents of babies on different care pathways (eg, moving from LNU to NICU and vice versa). We will attempt to ensure diversity of participants in relation to maternal age, ethnicity, socioeconomic status and educational background. A further 20 will be ‘real-time’ interviews with clinicians and parents caring for a baby currently receiving neonatal care. These will be conducted in two operational delivery networks, situated in the West and East Midlands, the two neonatal networks closest to the study centre, for practical reasons. For these interviews, we will also include clinicians of different ethnic backgrounds, ages and sexes.

The qualitative data will be analysed using the constant comparative method^34^ assisted by NVivo software. A coding scheme developed through detailed engagement with the data will be used to process the dataset systematically by assigning each section of text to a category, according to the category specifications. Parent panel members will be invited to comment on the face validity of the analysis of qualitative data.

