Most ODNs have a defined gestational age cut-off, below which they aim to provide care in an NICU.^3 10^ However, these criteria differ between networks and are often not adhered to. Currently, care pathways for babies born at 27–31 weeks gestation are undefined and their management is spread, often arbitrarily between NICU and LNU. While there is some evidence to suggest that morbidity profiles (based on common major morbidities such as necrotising enterocolitis, retinopathy of prematurity and bronchopulmonary dysplasia) for the total group of babies born at 27–31 weeks gestation^6^ is similar between LNU and NICU, it remains unknown whether location of care and/or birth, makes a difference to gestation-specific outcomes. Our research will determine whether the type of neonatal unit in the hospital of birth influences outcomes for babies born at 27–31 weeks gestation, and if so, at which set point within this gestational age range care can equitably be provided in either LNU or NICU.

Presently, most pregnant women who want a hospital birth are advised to choose antenatal care and delivery in a hospital in their area,^11^ which may have NICU, LNU or SCBU facilities. With the advent of Choose and Book,^12^ this may be changing. Place of booking may also partly be determined by the anticipated degree of illness or complexity of care required for either mother or baby, if that can be predicted. However, for most women at the time of booking for pregnancy care, these risks are unknown and unpredictable. Women in threatened preterm labour at 27–31 weeks gestation will generally attend their hospital of booking for assessment or one closest to them at the time. Many will, therefore, deliver there, regardless of the type of neonatal care that can be offered. Babies that are inevitably born into an SCBU setting in this gestational age range are usually transferred ex-utero to an LNU or NICU for ongoing care. They may be returned to an SCBU from an NICU or LNU for ‘step-down’ hospital care if this is the unit closest to the mother’s home, they are usually older than 32 weeks gestation and better, but not yet ready for discharge home. Generally, transfers that do occur between hospitals, whether for a mother before delivery or for her baby after birth, and are determined by care requirements, and by cot capacity and adequacy of neonatal nurse and medical staffing.

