Matching to account for measured confounding: We will use matching to construct a balanced sample of babies who were born in NICU or LNU based on observed characteristics, assuming that these groups do not differ in relevant unobservable characteristics so that the differences in outcomes between them may be attributed to the location of birth. We will use propensity scores (PS), which are predicted probabilities of the relevant observed covariates that would be expected to be equal for both groups if the conditional distribution is independent of whether the baby is born in an NICU or LNU.^23 24^ To compute the PS, a logistic model for place of birth will be fitted (LNU vs NICU). The independent variables will include a priori decided set of variables on the basis of expert and clinician input and/or variables associated with the type of unit at the place of birth. Based on previous literature^25 26^ and the data availability in NNRD, we will evaluate a relatively large number of covariates for this model including: gestational age, birth weight, sex of the baby, mothers’ ethnicity, use of antenatal steroids, 5 min Apgar score, deprivation, temperature at birth, maternal medical problems prior to this pregnancy and problems encountered during pregnancy. The selected variables are expected to influence either the place of birth or babies’ outcomes, but none of them would be expected to be influenced by whether the baby is born in an NICU or LNU as they are defined at baseline prior to or immediately after the birth. We believe that the model developed in the above steps will produce the PS given the observed set of covariates to produce balanced groups for the analyses; this means that babies who were born in NICUs and those who were born in LNUs with equal PS will have the same distributions of the observed covariates. After the PS is computed from the model, a matched sample will be created and the covariates will be compared between the groups in the matched sample to examine whether the balance has been achieved or not. If the sufficient balance is not achieved, the PS model will be modified and balance will be reassessed. We will investigate the range of estimated PS for both NICU and LNU babies to identify the region of common support. If there is no comparable NICU baby found in the LNU group, the analyses would produce biassed estimates by matching LNU babies with NICU babies with different characteristics. Therefore, observations not under common support should be dropped from the matching, but we will describe the characteristics of these babies in descriptive statistics. It is difficult to define the size of this matched sample at this stage. The sample size will be affected by how relevant it will be considered to the general population and will be reviewed by the study team. If required, other matching methods will also be applied, such as Mahalanobis distance matching and genetic matching.^27^

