
IVs to account for unmeasured confounding: Since matching is based on the assumption that the place of birth is independent of the potential outcomes conditional on the matching variables (also known as measured confounding). This requires that variables that affect both outcomes and the place of birth are observed and controlled in the matching algorithm. In our case, after matching the babies who were born in NICU or LNU on the basis of observed characteristics, it is possible that unobserved confounding variables still remain unbalanced between the two groups and the matching would result in biassed estimates of the effects of being born in NICU compared with LNU. Although we believe that the richness of our dataset makes the assumptions behind the matching plausible, we will complement our analyses using IVs.^28^ We will explore two-stage least squared regression (2SLS) models with exclusion restrictions that help us to explain variation in the types of unit the babies were born that is independent of outcomes. In the first stage, we will estimate the probability of a baby’s birth in NICU as a function of baby-level characteristics and IVs. The estimated probability of being born in an NICU will then be used in a second equation to estimate the effect of being born in an NICU on the outcomes of interest after controlling for a vector of observed baby-level characteristics. If the IVs are correct, the 2SLS method will generate unbiased estimates of the place of birth on babies’ outcomes.

In general, a variable is considered to be an IV, if it is (1) associated with the type of unit at birth (NICU vs LNU), (2) does not have direct effect on the outcome (say mortality) and (3) is independent of unmeasured confounders (UCs) but may be related to the measured confounders (MCs).^28 29^ The assumed relation of (IV) with outcome (4), type of unit at birth (NICU vs LNU), UCs and MCs can be described by the graph in figure 3.^30^

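### The controls named for the excess-distance instrument cover socioeconomic differences but not remoteness or urban-rural residence, so the 2SLS estimate may be biased in either direction

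*Protocol article*

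**What the plan says.** All of this is in the Protocol article, mostly under Workstreams 1 and 3.

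- **Instrument.** It is introduced as "A potential IV, used in previous studies in the USA", and it "is the difference of the distances of the mother residential postal code to the nearest NICU and LNU postal codes (excess distance").
- **Exclusion restriction, condition (2).** It is stated as an assumption, and in terms of time rather than distance: "The assumption that the difference in travel times to either facility should not directly affect the outcomes" except through the unit of birth.
- **Independence, condition (3).** The article qualifies this itself: "because hospitals with NICUs tend to locate in select areas (ie, cities), mothers who live here may be different from those who do not". It puts that difference in socioeconomic terms and gives one remedy: "We attempt to address this issue by controlling for mothers’ occupation and deprivation".
- **Other controls.** The second stage estimates the NICU effect "after controlling for a vector of observed baby-level characteristics". That vector is not itemised. The covariate list given for the propensity score includes "gestational age, birth weight, sex of the baby, mothers’ ethnicity, use of antenatal steroids, 5 min Apgar score, deprivation, temperature at birth", together with maternal medical problems and problems in pregnancy. It has no distance, travel-time or urban-rural term.
- **Which hospital women reach.** The Background and rationale says that women in threatened preterm labour at these gestations "will generally attend their hospital of booking for assessment or one closest to them at the time".
- **Role.** Matching handles measured confounding, and the instrumental-variable analysis complements it. The same approaches serve the clinical and the cost-effectiveness workstreams.

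**The concern.** The article raises a geographic threat to its instrument and then answers only the socioeconomic part of it. Two other features of residence may follow the same geography.

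The first is remoteness, meaning how far the mother lives from the nearer of the two unit types. If women generally go to their booking hospital or the closest one, this distance may affect how soon they receive care, whatever the type of unit. The second is urban or rural residence itself, which may carry risk that deprivation and occupation do not capture.

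If either is correlated with excess distance and with death, given the variables in the model, the instrument reaches the outcome by a route other than place of birth. Any such leak is divided by the first-stage effect, so it is magnified. 2SLS is the only method the article names against unmeasured confounding, and a bias in it would carry through to the cost-effectiveness result.

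**Working it through.** **1. Study size.** The article expects about 6000 babies a year for five years: 6000 × 5 = 30 000, as it states. At its expected mortality of about 5%, that is 30 000 × 0.05 = 1500 deaths.

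**2. Do the named controls measure the missing features?** Occupation and deprivation are socioeconomic. The covariates listed for matching describe the baby, the pregnancy and the mother's background. None is a distance, a travel time or an urban-rural class. Some (antenatal steroids, Apgar score, temperature) may lie on a path from late arrival to death, so they could absorb part of a remoteness effect if they enter the 2SLS model.

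**3. How a leak is magnified.** Split births into halves near to and far from a NICU. With a true NICU effect of zero, the Wald ratio gives

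spurious NICU effect = −(far-minus-near mortality gap) ÷ (near-minus-far difference in the probability of NICU birth).

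The article gives neither quantity, so both are assumed:

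| Residual gap (points) | First stage 0.2 | First stage 0.4 | First stage 0.6 |
|---|---|---|---|
| 0.25 | −1.25 | −0.625 | −0.42 |
| 0.50 | −2.50 | −1.25 | −0.83 |
| 1.00 | −5.00 | −2.50 | −1.67 |

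A gap of the opposite sign reverses every entry. With 15 000 births per half, the standard error of the gap is √(2 × 0.05 × 0.95 ÷ 15 000) = 0.25 points. The chance that the near-far comparison is significant at two-sided 5% is then about 17%, 51% and 98% for the three gaps.

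**4. Does excess distance carry remoteness with it?** The documents give no map, so this was simulated. Taken from the article: 30 000 births, 5% mortality, 45 NICUs and 84 LNUs. Assumed: an invented 400 km square with 40 cities, 70% of births around cities, half the LNUs around cities, and NICU birth becoming less likely as excess distance grows. There were 40 maps per setting and the true NICU effect was zero. Deprivation was the only control; occupation and the baby-level covariates were not simulated. Mean 2SLS estimates, in percentage points (negative means apparent NICU benefit):

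| NICUs in cities | Mean correlation, excess v nearest-unit distance | No omitted path | +0.25 per 10 km | +0.5 per 10 km | +1.0 per 10 km | City +1 point |
|---|---|---|---|---|---|---|
| 30% | 0.05 | −0.05 | −0.10 | −0.15 | −0.28 | −0.01 |
| 60% | 0.13 | −0.07 | −0.21 | −0.32 | −0.58 | +0.20 |
| 90% | 0.24 | +0.02 | −0.23 | −0.49 | −1.00 | +0.43 |

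The correlation in single maps ran from −0.32 to +0.45. In the nine gradient settings a false NICU benefit was declared in 5% to 53% of runs. In the three city-risk settings a false NICU harm was declared in 0% to 12%.

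With 40 runs, the Monte Carlo error at 53% is √(0.53 × 0.47 ÷ 40) = 8 points, and at 5% it is √(0.05 × 0.95 ÷ 40) = 3 points. The smallest shifts are no larger than the drift seen with no omitted path, so the low end of the range is not distinguishable from no bias.

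**5. Adding the missing terms.** With nearest-unit distance and a city indicator in both stages, the mean was −0.01 to −0.09 in the gradient settings (rejection 3% to 7%) and −0.05 to −0.09 in the city-risk settings (rejection 3% to 5%). A mean of −0.09 also occurred with no omitted path. This is a best case, because the added terms have exactly the form that generated the deaths.

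**The case against.** The strongest reply is that the plan is tentative and the model incomplete as shown. The instrument is only a candidate, 2SLS is to be explored as a complement to matching, and the full covariate set may sit in a document not shown. That stands as far as severity goes. It does not answer the point, because the article itself raises the city problem and commits to a specific remedy, and that remedy covers only part of it.

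A reader might go further and infer that excess distance must stay tied to absolute distance, and that 2SLS will therefore show a NICU benefit that does not exist. The documents do not support this:

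- Taking a difference of two distances removes part of any common remoteness. What remains depends on where units and mothers are; in the simulation the link was weak on average and negative on some maps.
- Nothing in the article says that remoteness raises mortality among admitted babies. Its remark on the closest hospital concerns where women go, not how babies fare.
- Two obvious routes are narrowed. Antenatal steroid use is a listed covariate. The population is babies born in a hospital with an LNU or NICU, which leaves birth before arrival largely outside it.
- Excess risk in cities pushes mostly the other way, towards false NICU harm.

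It would also be wrong to read occupation and deprivation as the only controls in the model. They are the only remedy named for city location; a baby-level vector enters as well, though nothing listed measures distance or rurality.

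**Conclusion.** The point holds in a limited form. The article concedes that NICU location is not random across places, treats the consequence as socioeconomic, and names controls that measure neither remoteness nor urban-rural residence. Conditions (2) and (3) are not secured against those features, and the 2SLS estimate may be biased in either direction.

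Size and sign cannot be fixed from the documents. Under the assumed maps, the range runs from a mean spurious benefit of 1.00 points, which is one fifth of the expected 5% mortality, through shifts too small to detect, to a spurious harm of 0.43 points. These figures rest on invented geography, assumed mortality gradients and control for deprivation alone; listed covariates such as steroids could reduce them. This is a weakness in a supporting analysis that a small change would mend, not a defect that undermines the study.

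**What to change.** In the instrumental-variable text under Workstreams 1 and 3, where occupation and deprivation are named, add two terms to both 2SLS stages:

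1. distance (or travel time) from the mother's residence to the nearest NICU or LNU, whichever is closer, in the same metric as the instrument;
2. an urban-rural class of that residence.

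Report 2SLS with and without these terms. Treat a material change in the point estimate as evidence that the instrument is sensitive to geography. Loss of significance alone should not count, since the added terms widen the interval.

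The cost is small. The nearest-unit distance is the smaller of the two distances already needed for the instrument. The urban-rural class needs a look-up from the residence postcode. Precision falls slightly: in a separate simulation of 30 000 births on a simpler assumed geography, adding distance alone raised the standard error from 0.55 to 0.59 points (0.59 ÷ 0.55 = 1.07, about 7%). The further cost of the urban-rural term was not measured there.

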**Methods:**

In this mixed-methods study, our primary objective is to assess, for babies born at 27–31 weeks gestation and admitted to a neonatal unit in England, whether care in an NICU vs an LNU impacts on survival and key morbidities (up to age 1 year), at each gestational age in weeks. Routinely recorded data extracted from real-time, point-of-care patient management systems held in the National Neonatal Research Database, Hospital Episode Statistics and Office for National Statistics, for January 2014 to December 2018, will be analysed. Secondary objectives are to assess (1) whether differences in care provided, rather than a focus on LNU/NICU designation, drives gestation-specific outcomes, (2) where care is most cost-effective and (3) what parents’ and clinicians' perspectives are on place of care, and how these could guide clinical decision-making. Our findings will be used to develop recommendations, in collaboration with national bodies, to inform clinical practice, commissioning and policy-making. The project is supported by a parent advisory panel and a study steering committee.

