## Background and rationale

Specialised services for babies in England are delivered by neonatal units managed through Operational Delivery Networks.^1^ These are geographical groupings of neonatal units working together in care pathways, and comprise units that are designated as neonatal intensive care units (NICUs), local neonatal units (LNUs) and special care baby units (SCBUs).^2 3^ There were 15 operational delivery networks (ODNs) in England in 2018.^4^ NICUs are located within centres that have specialist obstetric and fetomaternal medicine services; they have staff and resources to provide tertiary level care for babies of all gestational ages with a wide range and complexity of conditions. LNUs provide care for babies within their local catchment area; they are able to provide emergency, short-term intensive care but are not resourced to provide long-term intensive care. SCBUs provide the lowest intensity of care usually for babies born >32 weeks gestation.

Caring for babies born at 23–26 weeks gestation in an NICU improves survival to discharge. This is now shaping policy for this category of babies.^5–7^ However, there is no evidence to guide the location of care for the next most vulnerable group of babies born between 27+0 and 31+6 weeks gestation (hereafter called ‘born at 27–31 weeks’). This is an important group, accounting for around four times the throughput in neonatal units compared with those born at 23–26 weeks gestation,^8^ representing ~12% of all viable preterm babies born in England in 2013.^9^

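### Within each HRG level the costing gives a NICU day and an LNU day the same price, so any same-level cost difference between the two settings is zero by assumption

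*Protocol article*

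**What the plan says.** The second of the secondary objectives in the Abstract (Methods) is to find "where care is most cost-effective". The costing rule is in Workstreams 1 and 3, under the paragraph on healthcare costs and cost-effectiveness, and in Table 1.

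- Standard care is costed by level of care, using six HRGs. Each HRG has "a unit cost that gives the average cost to the NHS of providing defined services to NHS patients in England".
- On the source: "Unit costs used in our economic evaluation will be extracted from the NHS Reference Costs 2017/2018". Table 1 gives one figure per HRG and has no NICU or LNU column.
- On the formula, for standard care in either type of unit: "unit costs will be multiplied by the number of days using different levels of care".
- Six items (nitric oxide, surfactant, parenteral nutrition, ultrasound, transfusion, palivizumab) are costed on top. Literature and selected hospital finance departments are named as sources for these items only, not for the care day.
- Surgery stays inside the HRG price.
- The costs then enter an incremental NICU-LNU analysis in a net-benefit framework.

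Of NICUs, Background and rationale says that "they have staff and resources to provide tertiary level care for babies of all gestational ages with a wide range and complexity of conditions". It describes LNUs as able to give short-term, emergency intensive care but without the resources for prolonged intensive care.

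**The concern.** A single national price per level is harmless when the compared options are delivered in similar units. Here the type of unit is the comparison. If the same level of care takes different staffing or overheads in the two settings, that difference belongs to the quantity being estimated, and this rule removes it. A larger cohort does not help, because the error is in the price and not in the sampling.

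The stakes come from the plan's own reasoning. The Background argues that if clinical outcomes do not differ between settings, cost-effectiveness and family satisfaction should decide where services are delivered. In that case the incremental cost carries much of the conclusion, and the results are to feed national recommendations. The Background also wants to avoid placing less sick babies in a NICU without need. For a baby who would have the same days at the same levels in either setting, the rule returns no difference in standard-care cost, whatever the true costs are.

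**Working it through.** The plan states no total cost or cost difference, so there is no figure to reproduce. The check applies its formula to assumed stays.

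**Inputs from Table 1 (per day):** "Neonatal critical care, intensive care" £1445; "Neonatal critical care, high dependency care" £925; special care £605 with the carer not resident and £435 with the carer resident.

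**Assumed, because the documents give none:** days at each level, the percentage gap, and, at first, no transfers.

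**Step 1. What the rule returns for equal days.** Cost = sum over levels of (price × days). If both groups have the same days at each level, the standard-care difference is £0 by construction.

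**Step 2. The rule does not make the average day equal.** Take two 51-day stays.
- 8 intensive, 12 high-dependency, 28 special (not resident), 3 special (resident): 11,560 + 11,100 + 16,940 + 1,305 = £40,905, or £802 per day.
- 6, 12, 30 and 3 days respectively: 8,670 + 11,100 + 18,150 + 1,305 = £39,225, or £769 per day.

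The difference is £1,680, all of it from level mix. Only the within-level difference is suppressed.

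**Step 3. Size of a suppressed gap.** Assume 5 intensive, 10 high-dependency and 30 special-care days: 5 × 1445 + 10 × 925 + 30 × 605 = 7,225 + 9,250 + 18,150 = £34,625.
- 10% gap on every day: 0.10 × 34,625 = £3,462.50, about £3,460 per baby.
- 10% gap on intensive and high-dependency days only: 0.10 × (7,225 + 9,250) = 0.10 × 16,475 = £1,647.50, about £1,650 per baby.

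For other assumed stays, a 10% gap on every day gives:

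| Stay (intensive / high-dependency / special not resident / special resident) | Cost at Table 1 prices | 10% gap |
|---|---|---|
| 3 / 7 / 30 / 3 (43 days) | £30,265 | about £3,030 |
| 6 / 12 / 30 / 3 (51 days) | £39,225 | about £3,920 |
| 12 / 18 / 30 / 3 (63 days) | £53,445 | about £5,340 |

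**Step 4. Effect of transfers.** Groups are defined by place of birth, and babies move. Let r be the within-level NICU:LNU price ratio, with the LNU price held at Table 1. Let N be the mean NICU-delivered days at a level in each birth group. Then

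incremental cost(r) = incremental cost(1) + (r − 1) × sum over levels of price × (N in NICU-born − N in LNU-born).

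The gap acts only on the difference between groups in days delivered by NICUs. Step 3 is the limiting case in which every day is spent in the birth unit type; any crossover shrinks it.

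**Step 5. A threshold in practice.** In the Step 2 example, with the first stay in NICU, the second in LNU and no transfers, the incremental cost is zero when r = 39,225 / 40,905 = 0.959. A same-level NICU day about 4% cheaper would remove the £1,680. This shows how to read such a ratio; it is not a prediction for this cohort.

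**The case against.** The strongest defence is that national-average unit costs are a usual choice for an NHS perspective, and the plan declares both perspective and source. HRGs are meant to group clinically similar care, so level of care already captures much of the difference in complexity. The article condenses a fuller plan and commits to technology-appraisal guidance, so sensitivity analyses may exist elsewhere. Resource use is to be shown separately from costs, so others could re-price it.

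Much of this stands. The base-case choice is defensible, nothing contradicts itself, and the absence of a named sensitivity analysis is not the point. What remains is a stated rule: one price per level for both arms of a comparison between unit types, with local cost data directed only at procedures.

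Three stronger readings are tempting, and the documents do not support them.

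- A reader might infer that the plan removes every difference in day cost. It does not: Table 1 runs from £435 to £1445 by level, and length of stay, transport (£1159) and the six added items can all differ.
- A reader might infer a bias equal to the full price gap over the whole stay. The groups are defined by birth unit, and the Background describes transfers between units and step-down to SCBUs.
- A reader might turn the gap into a cost per life saved and conclude that the result would reverse. With an assumed 1-point mortality difference, 3,462.50 / 0.01 = £346,250, but that difference is assumed too. The Background says the settings are resourced differently; it does not say that a same-level day costs more or less in either.

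**Conclusion.** The concern holds within HRG levels. The plan assumes equal NICU and LNU prices for a day at a given level, so its incremental cost reflects only level mix, length of stay, transport and the listed procedures. This is a limitation of a reasonable costing choice, and it bears directly on the question asked. On the assumed 45-day stay, each 10% of within-level gap is worth at most about £3,460 per baby, or about £1,650 if confined to intensive and high-dependency days, before transfers reduce either figure. These amounts rest on assumed day counts and an assumed gap; only the prices come from the plan. Whether the value-for-money conclusion is sensitive to this cannot be known until the days by level and by delivering unit are available. As planned, the conclusion would be conditional on equal within-level prices without saying so.

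**What to change.** Keep the national-average costing as the base case. Add to the health-economics plan:

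1. A pre-specified threshold analysis that varies the within-level NICU:LNU price ratio, applied to the unit that delivered each day and not to the birth unit. Fix the range and the scaling convention in advance (for example, LNU price held at Table 1 and NICU price scaled).
2. A report of the ratio at which the net-benefit conclusion reverses, or a statement that it does not reverse within the range.
3. A value-for-money conclusion worded as conditional on that ratio.

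This uses the daily-care and transfer records already planned and needs no new data. The cost is a little more analysis and a less definite conclusion.

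Day costs by setting from finance departments should be an optional scenario only. NICUs treat all gestations and surgery sits inside the HRG price, so such figures could bring in case-mix differences that the matching and instrumental-variable analyses are meant to remove.
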